## Abstract

**Background:**

Non-alcoholic fatty liver disease (NAFLD) is rapidly increasing alongside overweight and obesity, not only in adults but also in children and adolescents. It is unknown what impact the development of NAFLD in childhood may have in later life. The importance of early detection and treatment lies in its potential for progression to cirrhosis, liver cancer and liver-related death, as well as its associated extrahepatic comorbidities. Vibration-Controlled Transient Elastography (VCTE) with Controlled Attenuation Parameter (CAP) is an effective, non-invasive and safe diagnostic method to estimate the degree of fibrosis and steatosis in the liver, but little is known about its applicability in the paediatric population.

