### Study aims

The study main aims are: 1) To assess the prevalence of significant liver fibrosis (LSM ≥6.5 kPa) using VCTE, and that of NAFLD (≥225 dB/m) using the CAP in children and adolescents; and 2) To determine the optimal cut-off points of the CAP to achieve maximum concordance with the MRI findings in the diagnosis of mild, moderate and severe liver steatosis in children and adolescents.

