### Specific outcome measures

Comparison of liver steatosis diagnosis accuracy between CAP by VCTE and Fatty Liver Index (FLI) in the general population aged ≥9 to ≤16 years.Comparison of liver fibrosis diagnosis accuracy between LSM by VCTE and two fibrosis scores (Pediatric NAFLD Fibrosis Index and Pediatric NAFLD Fibrosis Score) in the general population aged ≥9 to ≤16 years.Detection and structuring of the variables that constitute a specific biomarker for the paediatric-juvenile population that is capable of accurately determining the presence of hepatic steatosis.Correlation of liver steatosis diagnosis using CAP by VCTE, FLI and MRI, with the presence of lifestyles and socio-economic factors associated with NAFLD in the general population aged ≥9 to ≤16 years.Percentage of subjects with BMI ≥30 in the general population aged ≥9 to ≤16 years.Percentage of subjects with MetS according to the International Diabetes Federation (IDF) consensus criteria for children and adolescents [36] in the general population aged ≥9 to ≤16 years.

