LSM is performed in all patients using VCTE with the Fibroscan® (FS) system (Echosens, France). LSM is performed with S, M or XL probe following the Automatic Probe Selection tool available on the FS. The FS used is the 430 MINI. FS measures the hepatic elasticity of a cylinder approximately 1 cm in diameter by 4 cm in length [41]. FS transmits, via a probe, a vibration that propagates through the liver. The speed of propagation of the vibration correlates with the stiffness (in kPa) of the liver tissue and allows estimation of the fibrosis degree. In order for VCTE to be valid, 10 correct determinations with an interquartile range (IQR) <30 and a success rate >60% must be obtained. Significant liver fibrosis by VCTE is being defined by a LSM ≥6.5 kPa [13–16].Fibrosis scores/serum biomarkers: Pediatric NAFLD Fibrosis Index (PNFI) and Pediatric NAFLD Fibrosis Score (PNFS) are being used to estimate fibrosis degree. Significant liver fibrosis is being defined when the values of the different scores are above the following cut-offs, according to literature: PNFI ≥9, PNFS ≥13 [22, 23, 42, 43].

**Liver steatosis** is estimated using three methods: CAP, liver steatosis score and MRI.

CAP using VCTE is used to measure liver steatosis with the FS using either S, M or XL probe at the time of LSM. Liver steatosis is diagnosed when the value of CAP ≥225 dB/m [13–16].Liver steatosis is measured by the steatosis score Fatty Liver Index (FLI) which is based on: WC, BMI, TG and GGT [19]. Significant liver steatosis is defined when FLI ≥60 according to literature [44].Liver steatosis measured by MRI. It is performed using the Magneton Essenza 1.5 Tesla Aera system (SIEMENS), with the integration of Tim technology and Dot Engines (Day Optimizing through put Engines) application packages. The result obtained is the steatosis score or steatosis degree corresponding to the percentage of hepatocytes containing fatty vacuoles with respect to the hepatic fat fraction. Thus, a differentiation is made among mild steatosis (5–29% of hepatocytes affected), moderate steatosis (30–59% affected) and severe steatosis (more than 60% of hepatocytes affected). MRI is performed on all participants with altered VCTE results (≥6.5 kPa and/or ≥225 CAP) and 10% of participants with normal VCTE results (<6.5 kPa or <225 CAP).

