### Sample size calculation

The school population aged between 9 and 16 in Mataró stands at 11,503 individuals [45]. These are approximately equally distributed between the 4 groups: male/female between 9 to 12 and 13 to 16 years old.

We expect that 8% of this population will have NAFLD and 2% will have liver fibrosis. A sample size of 2,866 students will allow us to estimate a prevalence of NAFLD stratified by age (9–12, 13–16 years) and sex of 8%, with a precision of 2% in each stratum, and a prevalence of fibrosis of 2%, with a precision of 1% in each stratum. We anticipate that blood samples will be available in 50% of the sample and MRI in 70%. MRI will be offered to all LSM/CAP positive subjects (LSM ≥6.5 kPa / CAP ≥225 dB/m) and, randomly, to 10% of those with negative LSM/CAP (LSM <6.5 kPa / CAP <225 dB/m). This will add up to 1,433 blood tests and 424 MRIs.

With the proposed sample we can find a concordance of 80% with a precision of 4% using kappa indices, or an intraclass correlation coefficient of 0,8 with a precision of 2,5% (8% and 4% precision for kappa and ICC, respectively, using only 424 MRIs). This sample size has been calculated assuming a design effect of 20%, an alpha error of 5%, a power of 80% and bilateral contrasts.

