### Statistical analyses

Prevalences of NAFLD and fibrosis will be calculated using CAP ≥225dB/m and LSM ≥6.5kPa, respectively. They will be calculated by sex and age (9–12 and 13–16 years) and 95% confidence intervals will be provided.To determine the optimal CAP cut-off point that best fits the 4 MRI categories, the relationship between CAP and MRI will be explored graphically, CAP means for each MRI category will be compared by ANOVA, 2-to-2 ROC curves will be used, and a multi-class ROC curve will be used to obtain the overall area under the curve for the finally chosen points. In addition, dichotomous CAP classifications (normal/altered) will be compared with MRI levels using contingency tables and chi-square tests.To identify the variables related to NAFLD, multivariate models will be used using NAFLD as the dependent variable and possible risk and confounding factors as independent variables.Concordance between the diagnosis of NAFLD or fibrosis obtained by different methods (CAP vs FLI, LSM vs PNFI, LSM vs PNFS) will be assessed by kappa indices (when using the dichotomised version of these variables) and by the intraclass correlation coefficient (when using the continuous version of the variables). The best cut-off point in PNFI and PNFS will be chosen to detect fibrosis using LSM ≥6.5 kPa as the standard test in the diagnosis of fibrosis using ROC curves.The construction of the biomarker to detect the presence of steatosis in children and adolescents will be carried out using the coefficients of multivariate logistic regression models, where steatosis (CAP >225 dB/m) will be the dependent variable and the rest of the variables will be potential explanatory variables that may form part of the marker.

To take into account that participants come from selected schools, hierarchical models will be used when necessary. All tests will be bilateral, with a significance of 5%. We do not plan to use missing data imputation methods as we expect very few missings beyond those already considered. Stata17 statistical package will be used.

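### The steatosis biomarker is fitted to CAP >225 dB/m with no stated check against MRI, so it can only be shown to predict CAP positivity; the threshold also contradicts the ≥225 used elsewhere

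*Protocol article*

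**What the plan says.** Under Specific outcome measures, the protocol article promises "a specific biomarker for the paediatric-juvenile population that is capable of accurately determining the presence of hepatic steatosis". The Statistical analyses section builds it from the coefficients of multivariate logistic regression, in which "steatosis (CAP >225 dB/m) will be the dependent variable and the rest of the variables will be potential explanatory variables".

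Elsewhere CAP is the test under study. The second main aim is "To determine the optimal cut-off points of the CAP to achieve maximum concordance with the MRI findings", and the main outcome measures list both the accuracy of CAP against MRI and the choice of CAP cut-offs. The abstract says of elastography with CAP that "little is known about its applicability in the paediatric population". The Introduction calls MRI the more accurate method, though it also cites literature for the 225 dB/m cut-off.

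On the threshold, the measurement section says "Liver steatosis is diagnosed when the value of CAP ≥225 dB/m". The aims, visit schedule, main outcomes, sample size section and the prevalence sentence of the Statistical analyses section all use ≥225 as well. Only the biomarker sentence uses a strict inequality.

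**The concern.** The marker is meant to identify steatosis, but it is fitted to the result of a test whose cut-off the same study sets out to determine against MRI. If CAP misclassifies some children, the fitted coefficients describe who is CAP-positive, and good discrimination of CAP-positive from CAP-negative children does not establish that steatosis has been detected. The study will hold MRI results that could answer this, but the plan does not use them for the marker. What is at stake is the accuracy claim for a specific outcome; no main outcome is affected.

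Separately, a child measured at exactly 225 dB/m counts as having NAFLD in the prevalence estimate and as unaffected in the biomarker model.

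**Working it through.** **Inputs.** From Sample size calculation: 2,866 children, blood in 50%, MRI in 70%, 10% of negatives scanned, 1,433 blood tests, 424 MRIs, and "We expect that 8% of this population will have NAFLD and 2% will have liver fibrosis". From Statistical analyses: NAFLD prevalence is defined by CAP ≥225 dB/m, and no imputation is planned. The 8% is therefore an expected share of CAP-positive children.

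**1. The plan's own counts.**
- Blood: 0.5 × 2,866 = 1,433.
- MRI: 0.7 × 0.08 × 2,866 + 0.1 × 0.92 × 2,866 = 160.5 + 263.7 = 424.2.

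Both stated figures are reproduced, with 8% as the positive fraction and the 70% applied to positives only.

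**2. Data for an MRI check.** If blood and MRI availability are independent (assumption), half of the 424 have both: 0.5 × 424 = 212, of whom about 80 are CAP-positive and 132 CAP-negative. Among scanned children 160.5/424.2 = 38% are CAP-positive, against 8% in the sample. Unweighted accuracy figures from the scanned group would therefore not describe the school population.

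**3. MRI as the training outcome.** The documents do not give the number of MRI-positive children. Assume that 40% to 90% of scanned CAP-positives and 0% to 5% of scanned CAP-negatives are MRI-positive:
- Low end: 0.4 × 160.5 = 64.
- High end: 0.9 × 160.5 + 0.05 × 263.7 = 158.
- With blood as well: half of these, 32 to 79.

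This is fewer than the CAP events in step 5.

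**4. Share of CAP-positive children without steatosis.** The documents give no sensitivity or specificity for CAP. With 8% CAP-positive and an assumed sensitivity of 80%, solve 0.8p + (1 − Sp)(1 − p) = 0.08 for the true prevalence p:

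| Assumed specificity | p | False positives (1 − Sp)(1 − p) | Share of the 8% |
|---|---|---|---|
| 95% | 4.0% | 4.8% | 60% |
| 97% | 6.5% | 2.8% | 35% |
| 98% | 7.7% | 1.8% | 23% |

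The share depends heavily on a value the study has yet to estimate, so no single figure can be defended.

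**5. Events per candidate (supporting only).** Without imputation, a model with laboratory items uses complete cases: 0.08 × 1,433 = 115 events. Candidates listed under Data collection and measuring tools, with the blood count taken as one item: 5 socio-demographic, 8 personal history and habits, 6 family history, 5 lifestyle, 8 examination, 24 laboratory, HOMA and metabolic syndrome, 58 in all. Events per candidate: 115/58 = 2.0, or 115/50 = 2.3 for a round 50. For 50 parameters at 8% prevalence, an expected shrinkage factor of 0.9 needs 6,766, 3,253 or 1,845 children at an assumed Nagelkerke R² of 0.15, 0.30 or 0.50. All exceed 1,433.

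**The case against.** The strongest reply is that CAP is the only steatosis measure planned for every child, and that the article cites literature for its cut-off. Training on MRI would leave few events from a selectively scanned group. This stands: using CAP for development is defensible. The objection does not cover the missing comparison with MRI or the claim attached to the marker.

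It can also be said that the strict inequality is an editorial slip that touches only children at exactly 225 dB/m and leaves the prevalence unaffected. That stands as to size; the passages still conflict.

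Three stronger readings are tempting, but the documents do not support them:
- **That the marker would predict CAP error.** It predicts CAP positivity, part true steatosis and part misclassification, in an unknown mix.
- **That most cases would be false.** An assumed sensitivity of 80% and specificity of 90% at 8% true prevalence gives 0.064 + 0.092 = 15.6% CAP-positive, of whom 59% have no steatosis. That means about 0.156 × 1,433 = 224 events, so it cannot be combined with the 115 events that follow from 8% CAP-positive.
- **That a reported AUC would be inflated.** The text states no selection rule and no apparent AUC for the marker, and it calls the variables potential ones. Selection and internal validation may be set out in a full plan that is not shown.

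**Conclusion.** The point holds in a limited form. The article fixes CAP >225 dB/m as the biomarker outcome, promises a marker of hepatic steatosis, and states no check against the MRI reference that it uses for CAP itself. As written, the analysis supports a claim about CAP positivity only. How far that differs from steatosis cannot be read from the documents; the 23% to 60% range above rests on assumed accuracy. The threshold contradiction is plain from the text and needs no assumption, but its effect is probably small.

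The ratio of about two events per candidate assumes 8% CAP-positive, complete cases with blood, and all listed variables as candidates. It supports a careful fitting method and does not carry the point. The matter is worth correcting because the repair is cheap.

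**What to change.** 1. Change >225 to ≥225 in the biomarker sentence, to agree with the prevalence definition.
2. Keep CAP as the development outcome, describe the marker as predicting CAP positivity, and add a sensitivity analysis at the lowest CAP cut-off from the second main aim.
3. Evaluate the finished marker against MRI steatosis (5% or more, where the protocol's mild category begins) in scanned children with blood results. Weight for MRI sampling: about 1/0.1 = 10 for sampled CAP/LSM-negative children and about 1/0.7 = 1.4 for positives, if missed scans are unrelated to steatosis.
4. Preferably fit a penalised logistic model and report bootstrap optimism-corrected discrimination and calibration, resampling schools. The children in step 3 also belong to the development sample, so the MRI evaluation should be included in the bootstrap.

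No new data are needed, only wording and code. The downside is a small validation set. With 32 to 79 MRI-positive children and an assumed sensitivity of 80%, the unweighted 95% half-width is 1.96 × √(0.16/32) = 14 points down to 1.96 × √(0.16/79) = 9 points, and weighting is likely to widen it. The accuracy figure will probably also be less favourable than one judged against CAP.

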Visit 1 (V1): is carried out on all subjects, in the nurses’ offices of the educational centres. V1 includes: anamnesis, physical examination, VCTE to assess LSM and CAP, and collection of the completed socio-demographic and medical history questionnaire. After V1, all subjects are scheduled for Visit 2 and Visit 3. In addition, subjects with altered results (CAP ≥225 dB/m and/or LSM ≥ 6.5kPa) and 10% of subjects with normal results are referred to Visit 4. Lastly, subjects with suspected significant fibrosis (LSM ≥6.5 kPa) are referred to the Digestive Service of the Hospital Universitari Germans Trias i Pujol (HUGTP) for further evaluation (Visit 5).Visit 2 (V2): is conducted at the educational centres and consists on lifestyle assessment (Diet Quality estimation with the KIDMED index [31]), physical activity (PA) assessment with the Physical Activity Unified-7 item Screener (PAU-7S) [32], and sedentary behaviour [33], sleep duration [34], and sugar consumption assessment) through online self-reported questionnaires with the assistance of trained personnel.Visit 3 (V3): is performed in the Primary Care Centres corresponding to each subject. In V3, all subjects undergo blood sampling. The samples are analysed in the HUGTP laboratory.Visit 4 (V4): is performed in the Diagnostic Imaging Centres located within the area of the educational centres. MRIs are performed on all subjects with CAP ≥225 dB/m and/or LSM ≥6.5 kPa and 10% of participants with CAP <225 dB and/or LSM <6.5 kPa.Visit 5 (V5): is performed in the Digestive Service of the HUGTP. Subjects with suspected significant fibrosis (LSM ≥6.5 kPa) undergo the corresponding diagnostic tests and follow-up according the Clinical Practice Guideline for the Diagnosis and Treatment of NAFLD in Children [25].

Finally, all subjects (whether they obtain CAP ≥225 dB/m and/or LSM ≥6.5 kPa or CAP <225 dB/m and/or LSM <6.5 kPa), and especially those with NAFLD risk factors such as obesity, DM, MetS or risky alcohol consumption are counselled on lifestyle modifications by the health care professionals involved in the study [35]. They are also referred to their corresponding healthcare providers for management of these risk factors according to each centre’s own protocol (Fig 1).

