Anthropometric data: weight (kg), height (cm), Body Mass Index (BMI) [38–40], waist circumference (WC) [40] and thoracic circumference.Tanner’s pubertal stage: it classifies and divides pubertal changes into five successive stages, ranging from infant (grade I) to adult (grade V).Determination of blood pressure.**Analytical determination** is performed on all subjects, after 12 hours of fasting, at the Primary Care Centre. It includes:Blood count, glucose, glycosylated haemoglobin, basal insulin levels, total cholesterol, high-density lipoprotein (HDL), low-density lipoprotein (LDL), triglycerides (TG), aspartate transaminase (AST), alanine transaminase (ALT), gamma-glutamyl-transpeptidase (GGT), alkaline phosphatase (ALP), total bilirubin, sideremia, transferrin, transferrin saturation index, total protein, albumin, urea, creatinine, sodium, potassium, thyroid stimulating hormone (TSH) and tiroxine (T4).Determination of insulin resistance using the HOMA method: blood glucose (mmol/L) x insulin (mU/L)/22,5.

**Metabolic Syndrome (MetS)** is determined according to the IDF consensus criteria for children and adolescents [36]. These include a WC at the ≥90th percentile and the presence of 2 or more of the following variables: 1) TG ≥150 mg/dl, HDL <40 mg/dl. 2) Blood pressure ≥130/85 mmHg. 3) Blood glucose ≥100 mg/dl or previously diagnosed DM.

**Liver fibrosis** is estimated by two methods: LSM and liver fibrosis scores.

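### The expected loss of half the blood samples is counted but not treated as possible selection, so blood-based specific outcomes may not describe the general population

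*Protocol article*

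**What the plan says.** Blood is planned for everyone. Under Study design: "In V3, all subjects undergo blood sampling". Under Data collection and measuring tools, the analytical determination "is performed on all subjects, after 12 hours of fasting, at the Primary Care Centre". The Study design text makes this Visit 3. Table 1 as printed puts primary care centres under Visit 2. Either way it follows Visit 1, where VCTE and the physical examination are done at school.

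The Sample size calculation expects much less: "We anticipate that blood samples will be available in 50% of the sample and MRI in 70" per cent. It then gives the totals: "This will add up to 1,433 blood tests and 424 MRIs".

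The Statistical analyses section closes the subject: "We do not plan to use missing data imputation methods as we expect very few missings beyond those already considered". It mentions no weighting, comparison of children with and without blood, or sensitivity analysis.

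The Specific outcome measures include "Percentage of subjects with MetS according to the International Diabetes Federation (IDF) consensus criteria for children and adolescents", to be reported for the general population aged 9 to 16. CAP versus FLI and LSM versus PNFI and PNFS carry the same population label. The steatosis biomarker is described as for the paediatric-juvenile population.

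**The concern.** Counting a loss deals with precision. It does not deal with the question of which children are lost. Attending a second site after a 12-hour fast takes effort, and the family may already know the Visit 1 findings. Children with altered VCTE results are referred on, and those with obesity, diabetes or metabolic syndrome are singled out for counselling. Attendance could plausibly depend on adiposity, CAP, LSM or social class, although the article does not say that it does.

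If it does, complete-case proportions and kappas for the blood-based outcomes describe attenders. The Visit 1 measurements that could correct much of this are planned for every participant, and the stated rule makes no use of them for that purpose.

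**Working it through.** **1. The plan's own figures.**
- Blood: 0.50 × 2,866 = 1,433, as stated.
- Total sample: the binding criterion is "a prevalence of fibrosis of 2%, with a precision of 1% in each stratum". Per stratum, 1.96² × 0.02 × 0.98 / 0.01² = 752.9. With the finite population correction for 11,503/4 = 2,875.75 children, 752.9 / (1 + 752.9/2,875.75) = 596.7, rounded up to 597. Then 597 × 1.2 (design effect) × 4 strata = 2,865.6, or 2,866.

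So the sample size follows from the VCTE prevalence targets, and the 50% enters only afterwards, as a count.

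**2. Which outcomes need blood.**

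| Outcome | Blood needed? |
|---|---|
| LSM and CAP prevalence, CAP versus MRI, CAP cut-offs (all the main outcomes) | No |
| CAP versus FLI | Yes: FLI uses triglycerides and GGT |
| LSM versus PNFI, PNFS | Yes: listed as serum biomarkers |
| Metabolic syndrome percentage | In part: lipids and glucose, but only if waist is at or above the 90th percentile |
| Steatosis biomarker | Where blood values enter the model |

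**3. Is the available half random?** No random blood subsample is described. Sampling is intended for all, so the missing half must arise from non-attendance, refusal or failed sampling.

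**4. Size for a proportion that needs blood in every child.** The documents give no attendance pattern, so these inputs are assumptions: true proportion p = 5%, overall attendance 50%, affected children attending RR times as often as the rest.

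Observed proportion = p × RR / (1 + p × (RR − 1)).

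| RR | Observed |
|---|---|
| 0.5 | 0.025/0.975 = 2.6% |
| 0.8 | 0.040/0.990 = 4.0% |
| 1.25 | 0.0625/1.0125 = 6.2% |
| 1.5 | 0.075/1.025 = 7.3% |
| 2 | 0.100/1.050 = 9.5% |

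The 95% half-width at n = 1,433, ignoring the finite population correction, is 1.96 × √(1.2 × 0.05 × 0.95 / 1,433) = 1.2 percentage points. At the ends of this range the bias (−2.4 and +4.5 points) is well outside the interval. With no assumption about the missing half, an observed 5% is compatible with a true value from 0.5 × 5% = 2.5% to 2.5% + 50% = 52.5%.

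**5. Size for kappa, CAP versus FLI.** Assume 8% CAP-positive (the plan's expected NAFLD prevalence), and FLI with 60% sensitivity and 95% specificity against CAP (illustrative values). Kappa = (observed − chance agreement) / (1 − chance agreement).
- All children: (0.9220 − 0.8410) / (1 − 0.8410) = 0.51.
- CAP-positives attend twice as often, so prevalence among attenders is 0.16/1.08 = 14.8%: (0.8981 − 0.7593) / (1 − 0.7593) = 0.58.
- CAP-positives attend half as often, so prevalence is 0.04/0.96 = 4.2%: (0.9354 − 0.8915) / (1 − 0.8915) = 0.40.

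CAP is measured at Visit 1, so weighting on it would recover 0.51 in both cases.

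**6. Metabolic syndrome.** Waist at or above the 90th percentile is mandatory, and waist is part of the Visit 1 examination. Assume 10% of children are at or above it, attending R times as often as the rest, with 50% overall. Attendance in the high-waist group is 0.5R / (0.9 + 0.1R). Status is then unknown only in high-waist non-attenders:
- R = 0.5: attendance 26.3%, unknown 0.10 × 0.737 = 7.4% of the sample.
- R = 1.25: attendance 61.0%, unknown 3.9%.
- R = 2: attendance 90.9%, unknown 0.9%.

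If low-waist non-attenders are discarded instead, the percentage is multiplied by R / (0.9 + 0.1R): 0.53, 1.22 and 1.82 respectively. The article does not say which denominator will be used.

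**The case against.** **The sentence does not contradict the 50%.** A reader might set the expectation of few missing values against the expected loss of half the samples and call it a contradiction. The text does not support that, because it exempts losses already considered. Nor does it rule out every missing-data method. It declines imputation and is silent on weighting. Both points stand. What remains is that the exempted loss was considered only as a number.

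**Detail belongs in the analysis plan.** The form of a weighting model, or a table of attenders and non-attenders, is commonly left out of an article. That is fair. However, this article takes a position on missing data and gives its reason, and the reason sets aside the one large loss.

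**Selection is not shown.** All children are scheduled for the blood visit whatever their VCTE result. Result-based referral concerns only Visits 4 and 5. Dependence of attendance on adiposity, results or social class is therefore possible but not documented, and its direction is unknown.

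**Not every measure is biased.** If attendance depends only on the reference status, the AUROC of PNFI or PNFS against LSM is unchanged. In the biomarker's logistic model, selection on the outcome alone moves the intercept and not the slopes. Bias in those quantities needs joint selection on outcome and predictors. Kappa and proportions are more exposed.

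**Metabolic syndrome.** A reader might infer that its prevalence will be overstated by 22% to 82%. That holds only if children whose waist already excludes the syndrome are dropped, and only if high-waist children attend more often. The documents establish neither.

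**Conclusion.** The point holds for the blood-based specific outcomes only. As written, the plan leads to complete-case analysis of a non-random half of the sample, with most of those results still labelled as describing the general population. A reader might extend this to the study's headline prevalences or to the CAP cut-offs. The documents do not support that, since no main outcome uses blood.

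Whether there is bias, in which direction and how large cannot be known from the article. Under the stated assumptions, a true 5% that needs blood in every child could read as 2.6% to 9.5%, and a kappa of 0.51 as 0.40 to 0.58. For metabolic syndrome the exposure is small if the waist criterion is applied to every child, and larger if it is applied only to those with blood.

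**What to change.** Replace the sentence in Statistical analyses with a rule for the anticipated blood loss:

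- Analyse blood-based outcomes with inverse-probability-of-attendance weights, or with multiple imputation, using age, sex, BMI, waist, CAP and LSM from Visit 1, and social class and school type from the sampling frame.
- Report complete-case results as a sensitivity analysis.
- Compare Visit 1 characteristics of children with and without blood.
- For metabolic syndrome, classify every child with waist below the 90th percentile as negative whether or not blood is available, and weight or impute only among those at or above it.

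The cost is wording and programming, because the variables are already collected. The downsides are somewhat wider intervals and reliance on a missing-at-random assumption given the Visit 1 data. Attendance driven by something not measured there would remain uncorrected.
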